## Abstract

**Rationale:**

Post-stroke fatigue (PSF) is a frequent problem in stroke survivors and often hinders their rehabilitation. PSF is difficult to treat, and pharmacological therapy is often ineffective. Transcranial direct current stimulation (tDCS) can modulate motor, sensory, cognitive and behavioral responses, as it alters neuronal activity by delivering a small amount of current via the scalp to the cortex, resulting in prolonged alterations to brain function. tDCS has been studied for the treatment of fatigue associated with other neurological diseases, namely, multiple sclerosis, Parkinson’s disease and post-polio syndrome.

**Aims:**

This proposed project will examine the effect of tDCS on PSF.

**Sample size estimates:**

We will recruit 156 participants aged 18 to 80 with chronic stroke and allocate them equally to two groups (i.e., *n* = 78 per group).

**Methods and design:**

This proposed project will be a double-blind randomized control trial. The participants will be randomly divided into two groups. The control group will receive sham tDCS, and the treatment group will receive active tDCS. The latter treatment will involve application of a constant 2-mA current via one 5 × 5-cm anodal electrode positioned on the scalp over the C3 or C4 positions (motor cortex) of the lesioned hemisphere and one cathodal electrode positioned at the ipsilateral shoulder in two 20-min sessions per day for 5 days. The period of follow-up will be 4 weeks.

**Study outcome(s):**

The primary outcome measure will be a change in fatigue severity, as measured using the modified fatigue impact scale (MFIS). The participants’ scores on the MFIS (total score and physical, cognitive and psychosocial subscores) will be collected before treatment (T0), after 10 treatment sessions, i.e., 1 day after the fifth treatment day (T1), and 1 week (T2), 2 weeks (T3) and 4 weeks (T4) thereafter. Both per-protocol analysis and intention-to-treat analysis will be performed.

**Discussion:**

This proposed project will provide proof-of-concept, i.e., demonstrate the benefits of tDCS for the treatment of PSF. The beneficiaries are the subjects participated in the study. This will stimulate further research to optimize tDCS parameters for the treatment of PSF.

**Clinical trial registration:**

www.Chictr.org.cn, identifier: ChiCTR2100052515.

## Introduction

Fatigue is defined as the “subjective lack of physical or mental energy to carry out usual and desired activities as perceived by the patient” (1). Patients with fatigue may experience a devastating sense of tiredness, exhaustion or lack of energy during or after mental or motor activity. Fatigue is a common symptom of neurological disorders (2).

Post-stroke fatigue (PSF) is a common and chronic problem (3), with a frequency that varies from 23 to 85% (3–7). For many stroke patients with good recovery, PSF is the sole major disability (8). It was found that up to 40% of stroke patients reported PSF as the most troublesome consequence of stroke (3). PSF can hinder rehabilitation (5) and predicts reduced functional independence, risk of institutionalization, impairment of cognition, poor quality of life and increased mortality (9). Female sex, older age and previous stroke are clinical correlates of PSF (9). Other causes of PSF include sleep apnea (10) and depression (3, 11).

### Pathological mechanism of PSF

PSF is a complex problem with several contributing factors, many of which are not well understood. One theory holds that stroke may trigger biochemical imbalances, such as inflammatory responses, that generate fatigue in the early stages following stroke. Subsequently, neurophysiological and behavioral perturbations, such as beliefs about estimated action cost, may result in chronic PSF (11).

### Potential treatments that have been explored for alleviation of PSF

Potential pharmacological treatments for PSF, such as antidepressants, stimulants, vitamin D and wakefulness-promoting agents (e.g., modafinil), have failed to demonstrate significant benefits (12). Similarly, the efficacy of non-pharmacological treatments, such as low-intensity training, cognitive therapy, fatigue education, a mindfulness-based stress-reduction program, treatment of associated depression, Chinese herbs, correction of risk factors and adaptation of activities, remains unproven (13).

### Nature of transcranial direct current stimulation (tDCS)

tDCS can regulate sensory, cognitive, motor and behavioral responses (14), as it involves the application of a small amount of current to the cortex that regulates the activity of neurons and induces protracted after-effects in brain function. During tDCS, an anodal electrode is positioned over the targeted area and a cathodal electrode is positioned on a different part of the scalp or another body part, such as the shoulder. Importantly, tDCS does not cause severe adverse effects and is considered to be safe (15) and is a cost-effective and portable technique for neuromodulation (16).

Diverse effects on brain excitability can be achieved via tDCS, depending on the intensity, polarity and duration of the applied electric current. tDCS is a technique that in the short term is capable of modulating the resting potential of the membrane and in the long term of inducing for example functional plastic changes in the networks such as an increase or decrease in synaptic efficacy (17, 18).

The immediate effects of tDCS are caused by the modulation of resting membrane potential, whereas its long-lasting after-effects are due to the induction of enduring depression and potentiation (19). At the single-neuron level, tDCS generates glutamatergic plasticity that modulates the function of various ion channels and of neurotransmitters such as brain-derived neurotrophic factor and *N*-methyl-d-aspartate glutamate (19). In summary, tDCS can modulate neuronal excitability and induce prolonged functional changes in the brain (20). Stimulation of different levels of the neuromotor control system affects neuronal circuits in stroke patients, which causes neuroplastic changes. This reorganizes the damaged brain and produces improvements in function (19).

### Effects of tDCS in stroke patients

There is growing interest in tDCS as a treatment to facilitate stroke recovery, and small-scale clinical trials have suggested that tDCS can be effective in the treatment of various motor and non-motor dysfunctions in stroke patients. For example, tDCS has been found to improve the capacity for activities of daily living (21), swallowing function (22), gait training (23), motor learning (24), visuospatial neglect (25), central pain (26), verbal learning (27) and depression (28) in stroke patients. tDCS may be more effective in patients with stroke with mild-to-moderate impairments than in those with major impairments (29).

### Effects of tDCS in patients with PSF

An open-label trial of two sessions of tDCS per week for 5–6 weeks in 10 stroke patients did not result in any changes in PSF (30). Another recent clinical trial on 30 patients with PSF showed that compared with sham stimulation, one session of anodal tDCS over the bilateral primary motor cortex reduced symptoms of PSF for up to 7 days following treatment (31). One randomized control trial revealed no add-on effect of six sessions of tDCS on fatigue in 74 chronic stroke patients (32). Another randomized control trial of 6 sessions of tDCS per week for 4 weeks in 60 stroke patients reduced fatigue (33). Finally, there is an ongoing trial of six sessions of tDCS in 100 patients with PSF (34).

### tDCS for treatment of fatigue related to neurological disease

tDCS has been explored as a potential treatment for fatigue associated with other neurological diseases, namely, multiple sclerosis (MS), Parkinson’s disease and post-polio syndrome. For example, in a series of studies involving more than 50 patients with MS who received 5 sessions of tDCS applied over the motor cortex (35) or the somatosensory cortex (36, 37), results showed tDCS treatment led to a reduction of fatigue symptoms (35–37) and the improvement might persist up to 3 weeks (35). In a fourth study, 27 patients with MS were given 20 sessions of tDCS over the left dorsolateral prefrontal cortex, which which led to a decrease in their fatigue symptoms (37). In a fifth study, 17 patients with MS were given 10 sessions of random noise stimulation over the primary motor cortex, which led to a decrease in their fatigue symptoms (38). In two studies on patients with post-polio fatigue, 10 (39) and 15 (40) daily sessions of tDCS were found to decrease patients’ fatigue symptoms. In a clinical trial involving 23 patients with Parkinson’s disease, eight daily sessions of tDCS were found to decrease patients’ fatigue symptoms (41). Crucially, mild side effects (headache and tingling sensations) but no serious side-effects have been reported in the above-mentioned studies.

It has been suggested that three neurophysiological mechanisms underlie central fatigue: slowed conduction in central motor pathways, resulting in decreased recruitment of spinal motoneurons; blockage of conduction at Ranvier’s nodes; and impairment in the prefrontal cortex, which is responsible for motor planning (35). tDCS may alleviate PSF through several mechanisms. First, tDCS may restore activation in prefrontal and motor areas (35). Second, tDCS may improve connectivity between motor and frontal areas and the thalamus (35). Third, tDCS may increase positive mood and alleviate depressive symptoms (41).

In a recent review the effect of tDCS on fatigue in neurological disorders, 42 studies were identified. These studies included a total of 994 participants. Amongst these 42 studies, five of them, involving 290 subjects, examined the effect of tDCS in PSF. In 36 out of 42 (85.7%) of studies reported an improvement in fatigue scores in the tDCS group. Side effects of tDCS are usually mild (42). Hence tDCS proves to have a promising simple, low-cost, portable, non-invasive and risk-free procedure for reducing fatigue symptoms in alleviating PSF. The objective of this proposed project will be to examine the effect of tDCS on PSF. We hypothesize that active tDCS is more effective than sham tDCS.

## Methods

### Design

A double-blind randomized control trial of stroke survivors (Figure 1).

**Figure 1 fig1:**
[figure not shown]
Flow chart of the study.

### Patient population

Patients with chronic stroke will be recruited from the Neurology Unit of the Prince of Wales Hospital and the rehabilitation wards of Shatin Hospital (both in Hong Kong) and from the Hong Kong community through newspaper advertisements and word of mouth. A research assistant will visit the above facilities weekly to identify all eligible patients and obtain their written consent.

### Inclusion and exclusion criteria

The *inclusion criteria* will be (1) either sex; (2) aged 18–80; (3) any level of literacy or education; (4) a history of stroke confirmed by an brain imaging examination such as a CT scan or Magnetic Resonance Imaging; (5) able to speak ethnic Chinese and Cantonese; (6) willing and able to give informed consent; and (6) presence of PSF (a Fatigue Severity Scale [FSS] score of 4.0 or more) (43–45). The cut-off score of 4.0 was chosen since it the most commonly used cut-off score. In a recent systematic review of 31 studies using FSS to examine the prevalence of PSF, all of them reported a cut-off point of 4 or more (46).

The *exclusion criteria* will be (1) acute and subacute stroke (≤6 months after onset); (2) a history of depression (self-report or a Beck Depression Inventory (BDI) – II) (47) score ≥ 14; (3) a presence of schizophrenia, bipolar affective disorder, and/or substance/alcohol dependence/abuse; (4) a history of any neurological disorder (except stroke); (5) a history of sleep apnea, narcolepsy, hypothyroidism, heart failure, chronic obstructive pulmonary disease or cancer; (6) a history of unexplained spells of fainting; (7) current pregnancy; (8) a history of neurosurgery; (9) presence of dementia, defined as a Hong Kong version of the Montreal Cognitive Assessment (MoCA) score of less than 19 (48); (10) presence of aphasia, defined as a score > 0 in the best language instructions item of the National Institute of Health Stroke Scale (NIHSS) (49); (11) presence of major depression, as confirmed by a research assistant using the Structured Clinical Interview for Diagnostic and Statistical Manual (DSM) – Fourth Edition (SCID-DSMIV) (50) and according to the DSM – Fifth Edition Diagnostic Criteria (51); (12) taking hypnotics or other medications that can cause fatigue; (13) taking antiepileptic or other medications that can weaken the effect of tDCS; (14) current or past use of tDCS; (15) contraindications to tDCS, e.g., skin damage at the proposed site of stimulation or presence of a pacemaker, a metal implant in the head or a medical device in the brain; and (16) participation in rehabilitative therapy or physical exercise program during the trial. The above criteria will be assessed by examination of patients’ medical record.

### Measurement overview

The data collection schedule is detailed in Table 1. The number of patients excluded and the reasons for their exclusion will be recorded. Data on sex, age, level of education, risk factors of vascular diseases (e.g., smoking, hyperlipidemia, diabetes mellitus and hypertension), date of stroke onset and length of stay in rehabilitation facilities will be collected from all of the participants. Neurological impairment (i.e., the NIHSS total score data) at admission will be extracted from the stroke registry, which will be maintained by a full-time, well-trained research nurse who will also be responsible for administration of the NIHSS.

**Table 1 tab1:** Data collection schedule.

Study period	Screening	Treatment	EOT	FUV
**Visit**	**1**	**2–6**	**7**	**8–10**
**Weeks after Randomization**	**-2**	**1**	**1**	**2,3,5**
Review of inclusion / exclusion criteria	X			
Informed consent	X			
Demographics, vascular risk factors, stroke characteristics, previous treatment of PSF	X			
Montreal Cognitive Assessment	X			
MFIS, FFS, PSAE, BI, GDS, HADSA, SSQoL	X		X	X
tDCS		X		
Randomization	X			
tDCS adverse effects questionnaire		X	X	
Experience, preferences, concerns and belief on tDCS questionnaire			X	

Screen denotes Screening visit.

EOT denotes End of treatment.

FUV denotes Follow up visits.

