### Primary outcome measure

The MFIS will be administered before treatment (T0), after 10 treatment sessions (T1, 1 day after the fifth treatment day), and 1 week (T2), 2 weeks (T3) and 4 weeks (T4) thereafter (36), at the same time of day. The time window of administration will be adjusted to assess changes between time points (4 weeks for T0, 1 day for T1, 1 week for T2 and T3, and 2 weeks for T4). The participants and the research assistant who administers the MFIS will be blinded to the delivered treatment.

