### Sample size estimates

Statistical power was computed using Power Analysis & Sample Size 2005. We assumed that the standard deviation of the MFIS score at baseline will be 3.9 (60), that the sham stimulation will not cause any change in fatigue and that a decrease of at least 3.0 MFIS points will be clinically relevant (36). Hence, the effect size of tDCS will be (3.0/3.9 = 0.77). Given that such a large effect size is unusual in clinical contexts, we will instead use a more realistic effect size, i.e., 0.50. One pairwise comparison will be performed in the analysis of variance. A sample size of 63 per group (a total of 126 participants) will give rise to 80% power in identifying the main effect of tDCS (73). Thus, assuming a dropout rate of 20%, 156 (126/0.8) participants will be recruited.

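### Table 1 takes the only pre-treatment outcome scores at screening, in a column whose timing contradicts itself; paired tests against T0 are affected, the active-versus-sham comparison is not

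*Protocol article*

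**What the plan says.** Table 1 (Measurement overview) has one row for the outcome scales, "MFIS, FFS, PSAE, BI, GDS, HADSA, SSQoL"; I read the second and third entries as FSS and PASE. It is ticked at Screening (Visit 1), end of treatment (Visit 7) and follow-up (Visits 8 to 10). It is not ticked in the Treatment column (Visits 2 to 6).

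The timing row, "Weeks after Randomization", gives -2 for Screening, 1 for Treatment and for end of treatment, and 2, 3 and 5 for follow-up. The Screening column also ticks "Review of inclusion / exclusion criteria" and Randomization.

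The text on the primary outcome reads "The MFIS will be administered before treatment (T0), after 10 treatment sessions (T1, 1 day after the fifth treatment day", so T0 precedes treatment but has no stated day or visit. Recall windows are "4 weeks for T0, 1 day for T1, 1 week for T2 and T3, and 2 weeks for T4".

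Entry requires "presence of PSF (a Fatigue Severity Scale [FSS] score of 4.0 or more". The same section ends: "The above criteria will be assessed by examination of patients’ medical record". Baseline measures, however, has a research assistant administer the FSS.

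The Statistical analysis section uses baseline MFIS as covariate in the T1 comparison of active with sham. It also plans Bonferroni-corrected paired tests of baseline against later time points.

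**The concern.** A site following Table 1 would use the screening scores as T0. If the week heading is right, roughly two weeks or more of untreated time lie between that reading and the first stimulation, and any change in that interval is counted in T0-to-T1 change. The interval also falls outside the recall windows: T0 looks back four weeks from screening, and T1 covers one day.

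If the FSS reading that admits a participant is also the FSS baseline, participants were selected partly because that reading happened to be high. On average they will score lower next time without treatment.

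What is at stake is the paired tests against T0, and any reading of one arm's change from baseline as benefit. A further, smaller matter is the covariate: an older baseline may correlate less with T1.

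**Working it through.** **1. The plan's own figure.** Two-sided 5%, 80% power, effect size 0.50: n = 2(1.960 + 0.842)²/0.50² = 62.8, so 63 per group, as stated (power 80.1% by the normal formula, 79.5% by the t distribution). 126/0.8 = 157.5, against a stated 156; the difference is trivial. The formula uses no baseline correlation, so planned power does not depend on how good a covariate T0 is. The planned difference is 0.50 × 3.9 = 1.95 MFIS points.

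**2. Timing in Table 1.** The Screening column is headed week -2 counted from randomization and also ticks Randomization. Both cannot hold literally. If the heading is right, T0 precedes allocation by about two weeks. If the tick is right, treatment in week 1 could follow within days. The text only says before treatment, which fits either.

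**3. Regression to the mean on FSS, if the screening FSS decides entry.** Fall = (1 − ICC) × mean excess of those selected. ICC is 0.73 to 0.93 (Baseline measures). Assumed: screened mean 4.0, SD 1.5, so the cut-off lies at the mean.
- Mean excess = φ(0)/(1 − Φ(0)) × 1.5 = 0.798 × 1.5 = 1.20 points.
- ICC 0.93: 0.07 × 1.20 = 0.08 points.
- ICC 0.73: 0.27 × 1.20 = 0.32 points.

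**4. Carry-over to MFIS.** Nobody is selected on MFIS, so the effect is indirect: fall = 3.9 × λ × r × (1 − ICC), with λ = φ(z)/p. Inputs are p = 0.23 to 0.85 (the Introduction's frequency of PSF, assumed to be the share passing the cut-off), r = 0.62 to 0.84 (FSS with other fatigue scales, assumed to apply to MFIS) and the ICC range above.
- Smallest: 3.9 × 0.274 × 0.62 × 0.07 = 0.05 points.
- Largest: 3.9 × 1.320 × 0.84 × 0.27 = 1.17 points.

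This lets the two scales share transient error as strongly as true score, so it is close to an upper bound.

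**5. Effect on the tests.** Simulation with 63 per arm, selection on FSS, no treatment effect, 4,000 runs per row. The paired test is one test in the active arm at 5%, without Bonferroni correction.

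| p, r, ICC | Drift (assumed) | Mean sham change | Baseline-adjusted active − sham | Its rejection rate | Paired-test rejection rate |
|---|---|---|---|---|---|
| 0.85, 0.62, 0.93 | 0 | −0.05 | 0.006 | 4.8% | 6% |
| 0.50, 0.73, 0.83 | 0 | −0.39 | −0.003 | 5.0% | 27% |
| 0.23, 0.84, 0.73 | 0 | −1.16 | −0.005 | 5.8% | 91% |
| 0.85, 0.62, 0.93 | −0.5 | −0.55 | −0.006 | 4.4% | 84% |
| 0.50, 0.73, 0.83 | −0.5 | −0.89 | −0.004 | 5.3% | 88% |
| 0.23, 0.84, 0.73 | −0.5 | −1.66 | −0.010 | 4.7% | 99.8% |

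A constant drift cannot alter the between-arm test, so its rates in the last three rows are simply fresh draws of the first three. The 5.8% and 4.7% for the same inputs average 5.25%. The between-arm test stays close to nominal; the paired test does not.

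**6. Precision.** Residual variance after adjustment is proportional to 1 − r², where r is the T0-to-T1 MFIS correlation. The document gives neither r nor its decline with a longer gap, so no loss can be computed.

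**The case against.** The strongest reply is that this is a randomised, double-blind, sham-controlled trial with a between-arm hypothesis and a baseline-adjusted T1 comparison. A reader might infer from Table 1 that the estimated treatment effect is contaminated. It is not: drift and regression to the mean are common to both arms in expectation, and the simulated contrast is about zero. This stands in full.

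Other strong readings also fail:
- **Sample size.** The plan assumes "that the sham stimulation will not cause any change in fatigue". A fall under sham would contradict that sentence, but a fall common to both arms leaves the standardised difference of 0.50 intact.
- **Precision.** One could posit a correlation falling from 0.8 to 0.7 (residual variance 0.36 to 0.51, up 42%) or from 0.7 to 0.6 (0.51 to 0.64, up 25%). Those percentages only restate the assumed correlations. In chronic stroke, with a four-week recall window at T0, the true decline is unknown.
- **Age of the baseline.** A lag of two to three weeks is not established, because the week -2 column also ticks Randomization.
- **Same FSS reading for entry and baseline.** The medical-record sentence leaves unclear which reading decides entry, so regression to the mean is conditional.

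It can also be said that moving T0 to Visit 2 while randomizing at Visit 1 makes the covariate a post-randomization measurement and leaves some randomized participants without one. The first half is fair and must be handled in the fix. The second has little force here: the plan's intention-to-treat set requires at least one session, so everyone in it would have reached a T0 scheduled before that session.

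What survives is the contradictory timing and the effect on the paired tests.

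**Conclusion.** The point holds in limited form. The schedule fixes the only pre-treatment outcome scores at screening, and the column does not say consistently when that is relative to allocation and first stimulation. Nothing here biases the active-versus-sham comparison or lowers planned power.

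The paired tests against baseline are exposed to any untreated drift and, if the screening FSS decides entry, to a spurious FSS fall of about 0.08 to 0.32 points in each arm (assumed screened mean 4.0, SD 1.5). The indirect MFIS fall is 0.05 to 1.17 points in each arm, against a planned difference of 1.95. The top of that range combines the least favourable inputs and a generous assumption about shared error. The paired-test rejection rates are likewise illustrations under stated assumptions, for one uncorrected test. Any loss of covariate efficiency cannot be sized.

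Severity: minor to moderate.

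**What to change.** - In Table 1, keep the FSS at Visit 1 for eligibility only, and state which FSS reading decides entry.
- Schedule T0 (MFIS, FSS and the secondary scales) at Visit 2, before the first stimulation session, by the blinded assessor and at the time of day used at later visits. Name this as T0 under the primary and secondary outcomes.
- Correct Table 1 so that the Randomization tick and the week heading agree, with T0 completed before the allocation is acted on where feasible.
- Rest efficacy conclusions on the active-versus-sham contrast, and label the paired tests against baseline as descriptive.

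No visit is added. Visit 2 becomes longer (the MFIS alone takes 5 to 10 minutes and the SSQoL has 49 items), a real burden in fatigued participants, and the FSS is given once more. The move does not remove the mismatch between a four-week recall window at T0 and one day at T1. That mismatch also makes raw T0-to-T1 change hard to read, equally in both arms, and is another reason to keep the paired tests descriptive.
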